### Measures

Trait-level self-regulation will be assessed using the Brief Self-Control Scale (BSCS; Tangney et al., 2004), a short 13-item self-report instrument, psychometrically validated across 11 languages, and widely used as a robust proxy for dispositional self-regulatory capacity in adolescent and adult populations. Items are scored on a 5-point Likert scale ranging from 1 (*not at all like me*) to 5 (*very much like me*). The BSCS captures stable individual differences in the ability to modulate attention, emotion, impulses, and behavior, making it appropriate for detecting trait-level shifts in response to developmental scaffolding. A sample item is, “I wish I had more self-discipline.” The BSCS has demonstrated good internal consistency, (*α* = 0.83; Tangney et al., 2004). In a feasibility design, the objective is not to optimize latent factor modeling, but to index whether directional improvement is present at the level of standardized mean difference. Consequently, the BSCS will be administered one week prior to intervention onset and immediately post-intervention.

Trait-level social connectedness will be indexed using the Simple School Belonging Scale (SSBS; Whiting et al., 2017), a 10-item instrument that quantifies the subjective perception of being psychologically included, relationally valued, and socially embedded within the school’s peer ecology. A sample item is, “I feel like my ideas count at [school name].” School belonging is one of the most tightly coupled environmental predictors of both academic persistence and socioemotional well-being in adolescence. The SSBS functions as a proximal phenotype of this social connection, and changes in SSBS scores provide a trait-level marker of whether the intervention’s repeated micro-affordances generalized into durable, perceived relational embeddedness. The SSBS has also demonstrated strong internal consistency (*α* = 0.96; Whiting et al., 2017).

Momentary (state-level) regulations will be assessed through a daily, single-item Ecological Momentary Assessment (EMA) self-rating prompt delivered throughout the eight-week intervention phase. Adolescents are prompted with the question: “Right now, how effectively are you managing your emotions and behavior?” and respond on a 1–7 Likert scale (1 = *not effectively at all*, 7 = *very effectively*). Basically, this item is designed to capture real-time regulatory enactment rather than a retrospective or global self-assessment. Thus, EMA state trajectories recorded across Phase B provide a mechanism-level time-series dataset optimally structured for single-case Tau-U analysis.

All outcome indicators depend on student self-report, the protocol also incorporates two additional informant-based measures. Teacher behavioral ratings will be collected at pre- and post-intervention timepoints using a brief four-item adaptation of the Social Skills Improvement System (SSIS; Elliott et al., 2008) targeting observable classroom regulation behaviors (e.g., “This student recovers quickly from frustration”) and prosocial conduct (e.g., “This student initiates positive interactions with peers”). Items are rated on a 4-point frequency scale (1 = never, 4 = almost always) by the student’s primary classroom teacher. Parent or guardian reports will be collected using a parallel four-item brief form targeting home-context regulation and social behavior, administered via a secure online survey link at the same two timepoints. These informant sources provide convergent evidence from ecologically distinct observational contexts, reducing the sole reliance on student self-report and mitigating single-source inflation of perceived effects.

Implementation of fidelity will be captured via weekly counselor fidelity summaries. To minimize administrative burden and avoid interpretive drift, this documentation uses a structured, three-item binary checklist. The counselor simply records whether: (1) micro-nudges were opened at least four times during the week; (2) the student submitted at least one reflective note; and (3) the student concretely described at least one pro-social or regulation-aligned behavior. Counselors may optionally add a single-sentence contextual remark if relevant. These logs do not serve as qualitative data for phenomenology, but rather as direct fidelity evidence confirming that the designed mechanism was actively enacted.

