2	Micro-Choices	Identifying ‘choice points’ in daily routines	Student(s) can describe one moment/day where a micro-choice was made intentionally	
3	Regulation Moves	Using micro-regulation strategies in real time	Student(s) can report using at least one regulation move during a difficult moment	
4	Social Signals	Reading emotional/social cues in peers	Student(s) can identify one social cue observed in a peer interaction per day	Weeks 1–8: Daily EMA, weekly mini-session, fidelity log
5	Connection Behaviors	Performing pro-social action steps	Student(s) can report one specific pro-social action per day	
6	Real-World Practice	Applying skills in naturalistic school contexts	Student(s) can name one applied skill used in a school scenario that occurred	
7	Integration & Identity	Linking skills to values and identity	Student(s) can articulate one personal value and how a behavior reflected it	Week 8: BSCS/SSBS (post)
8	Transfer & Future Self	Projecting skills into future-oriented plans	Student(s) can describe one future scenario where learned skills will be used	

The AI augmentation is delivered through two channels. Channel 1 deploys daily micro-nudges aligned with the overarching weekly objective; these function as single-turn reflective invitations that increase the density of developmental prompts across the student’s daily ecological environment. Channel 2 consists of short-form (3–5 turn) micro-coaching dialogues, triggered either by voluntarily user initiation or automatically triggered following a 24-h lapse in engagement. Both channels are strictly reflective, offering no directive advice, clinical instruction, or evaluative feedback. The goal is to systematically increase the frequency with which the student monitors internal states, detects micro-choice moments, decodes social signals, and reflects on prosocial behaviors. Over the 8 weeks, this dual-channel architecture aims to expose the student to dozens of micro self-regulation enactments and relational affordances that incrementally accumulate to drive sustained and measurable developmental change.

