### Research design

The present study utilizes a feasibility-oriented outcome research design rather than a powered efficacy trial. The primary analytic purpose is to demonstrate whether an AI-augmented PYD delivery scaffold can be successfully implemented within standard school counseling environments. Furthermore, it seeks to observe whether the targeted micro–behavioral processes (awareness, micro–choices, regulation moves, prosocial micro-behaviors) the model is designed to generate occur under naturalistic conditions. Grounded in feasibility logic (de Boer et al., 2025), the primary inferential question is not whether the intervention outperforms existing protocols, but rather whether this model can be successfully implemented and whether it reliably produces mechanism-consistent enactments.

A mixed methodological structure is required because the targeted constructs, self-regulation and perceived social connectedness, have a dual ontological status: they exist simultaneously as trait markers (i.e., stable, longitudinal dispositions) and state performances (i.e., enacted, momentarily observable micro-behaviors). Quantitative data alone cannot verify state enactment; rather, process-embedded qualitative evidence is essential to determine whether actual behavioral practice occurred. Consequently, in this protocol, quantitative indices are utilized to capture directional change, while qualitative materials serve to continuously verify mechanism enactment in real time.

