### Data analysis strategy

The analytical framework of this study is structured to evaluate three outcomes: (a) trait-level directional movement, (b) state-level micro-trajectory change, and (c) mechanism enactment evidence. These three analytical layers correspond directly to the theoretical dimensions the intervention engages in disposition, enactment, and meaning-in-use. To assess trait-level shifts, pre- and post-intervention changes in the BSCS and SSBS will be quantified using a within-subject standardized mean difference, following Lakens’s (2013) generalized within-subject effect size formulation. This approach mitigates dependence on between-subject variability and is appropriate for feasibility designs wherein each participant serves as their own baseline control (Lakens, 2013, 2017). To robustly index the magnitude of directional movement, 95% confidence intervals will be calculated, despite traditional null-hypothesis significance testing not being required under feasibility logic.

State-level EMA sequences (Phase A baseline vs. Phase B intervention) will be analyzed using Tau-U with baseline trend correction. Importantly, correcting for baseline trend prevents inflated effect-size estimates that might otherwise be misattributed to intervention exposure rather than pre-existing directional drift. Tau-U allows non-overlap evaluation even with small samples and is currently the most methodologically defensible effect-size metric for SCED micro-regulation sequences. Qualitative data will be evaluated via reflexive thematic analysis, though explicitly restricted to mechanism verification rather than narrative phenomenology. Coding will be deductive and anchored to the weekly objective architecture.

Finally, to integrate the three evidence streams, a triangulation matrix will be constructed to map (a) trait-level shifts, (b) state-level effect estimates, and (c) qualitative mechanism evidence. The purpose of this synthesis is not to blend subjective narrative with statistical data, but to evaluate whether the targeted mechanism signal is reliably detectable across heterogeneous measurement modes. Methodological convergence across these domains confirms intervention feasibility, while signal divergence indicates a structural implementation malfunction.

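### The daily EMA item rates how well students feel they are managing, not regulatory enactment as the protocol states, so a Tau-U shift should not count as evidence of enactment

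*Protocol article*

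**What the plan says.** The Measures section describes a "daily, single-item Ecological Momentary Assessment (EMA) self-rating prompt". The question is "Right now, how effectively are you managing your emotions and behavior", on a 1–7 scale from not effective to very effective. The section then makes two claims for it: that "this item is designed to capture real-time regulatory enactment rather than a retrospective or global self-assessment", and that "EMA state trajectories recorded across Phase B provide a mechanism-level time-series dataset optimally structured for single-case Tau-U analysis".

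The Data analysis strategy section lists three outcomes: trait movement, state-level trajectory change, and evidence of mechanism enactment. It says these correspond, in that order, to "disposition, enactment, and meaning-in-use". The EMA and Tau-U layer is therefore the enactment layer. The section ends by saying that convergence of the three streams confirms feasibility and that divergence points to an implementation failure.

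The Research design section speaks differently. It describes state performances as "enacted, momentarily observable micro-behaviors", says that quantitative data cannot by themselves verify enactment, and gives that task to the qualitative material. One worked instance of an enacted behaviour is the Week 3 outcome in Table 1, where the student "can report using at least one regulation move during a difficult moment".

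**The concern.** A self-rating of how well one is managing differs from a record that one did something to regulate. A student in a calm moment can truthfully answer 7 with nothing enacted. A student who uses a strategy under strain may answer 4. The rating reflects both skill and situational demand, and no daily measure of demand is planned.

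Phase A is two weeks and Phase B is the following eight. If tests, peer events or the school calendar make the two phases differ in difficulty, Tau-U can change while enactment does not. The protocol makes the reliable production of mechanism-consistent enactments part of its primary inferential question, and it feeds the state result into the convergence judgement. A Tau-U shift read under the present label could therefore be counted as enactment, or its absence as a malfunction, when the item shows neither.

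**Working it through.** **1. Claim against item.** The document states no figure to reproduce here, so the first check is textual.

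| Element | Claimed in Measures | Present in the item? |
|---|---|---|
| Real-time, not retrospective or global | yes | yes: it asks about right now |
| Enactment (a behaviour carried out) | yes | no: it asks for perceived effectiveness |
| Whether there was something to regulate | implied by enactment | not asked |
| Whether a strategy was used | implied by enactment | not asked |

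Half of the quoted sentence holds and half does not.

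**2. Does trend correction help?** Take corrected Tau-U as (S_AB − S_A)/(n_A·n_B), where S_AB sums the signs of all A-to-B comparisons and S_A sums those within Phase A. S_A responds to drift inside the baseline. If demand is stable within each phase but differs between them, S_A averages zero and nothing is removed.

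**3. Possible size, from a mix of hard and easy days.** All inputs are assumptions: mean rating 4 on hard days and 6 on easy days, SD 1, independent days, 14 and 56 days, regulation unchanged. Let p_A and p_B be the shares of hard days. Only pairs of unlike days contribute on average, so

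expected Tau = [p_A(1 − p_B) − (1 − p_A)p_B] × G = (p_A − p_B) × G.

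On a continuous scale G = 2Φ(2/√2) − 1 = 0.84. With ratings rounded and limited to 1–7, G = 0.81.

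| Hard days, A → B | p_A − p_B | × 0.81 | × 0.84 | Simulated mean corrected Tau-U (4,000 students) |
|---|---|---|---|---|
| 50% → 40% | 0.10 | 0.08 | 0.08 | 0.08 |
| 50% → 30% | 0.20 | 0.16 | 0.17 | 0.16 |
| 50% → 20% | 0.30 | 0.24 | 0.25 | 0.24 |
| 30% → 50% | −0.20 | −0.16 | −0.17 | −0.17 |

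Corrected and uncorrected means agree to within about 0.001. Because G cannot exceed 1, the mean shift in this model can never exceed the change in the share of hard days, whatever the rating gap.

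**4. A second route.** If Phase B ratings shift by d standard deviations through demand alone, Tau = 2Φ(d/√2) − 1. For d = 0.25, 0.5 and 0.8 this gives 0.14, 0.28 and 0.43. Simulation on a rounded 1–7 scale (assumed mean 4.5, SD 1.3) gives 0.13–0.14, about 0.26 and 0.40. Harder days give values of about the same size with a negative sign.

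**5. Noise for comparison.** With no true shift, one student's Tau-U has an SD of about 0.17 at 14/56 points and about 0.20 at 10/40. The smaller shifts above would not stand out in a single student; a shift shared by all students would show in a group average.

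**6. Would restricting Tau-U to hard days cure it?** The Research design section asks for at least 10 Phase A points. With 14 baseline days and a 50% hard-day share, 14 × 0.5 = 7 hard days are expected, and the chance of 10 or more is (1001 + 364 + 91 + 14 + 1)/2^14 = 1471/16384 = 9%. At a 30% share it is 0.2%. At 60% compliance and a 50% share, about 14 × 0.5 × 0.6 = 4 remain.

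**The case against.** The best defence is that the protocol does not ask this item to prove enactment. The Research design section assigns verification to qualitative material and leaves directional change to the numbers. The analysis section lists enactment evidence as a stream separate from the state trajectory. The third fidelity item and the reflective notes look for described behaviours. Elsewhere the ratings are said to index momentary regulation states, which the item fits. The Limitations section already concedes school-calendar artefacts and disclaims causal attribution, and Tau-U is not one of the four feasibility thresholds.

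Much of this stands, and it rules out several stronger readings that a reader might infer:

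- *That the trial has no evidence of enactment.* The notes and fidelity log are intended to supply it.
- *That using a regulation move in a difficult moment is the protocol's definition of enactment.* That is the Week 3 outcome only; the general description is broader.
- *That the item measures something unrelated.* Perceived effectiveness is related to regulation; it is not its enactment.
- *That Tau-U will be inflated.* Phase B could be harder as easily as easier, and the documents give no data on either.

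What the defence does not repair is the text. The caution in Research design contradicts the claim in Measures, and the analysis section maps the EMA layer onto enactment. The Limitations concession concerns attribution of change to the intervention, not what the item measures. The state result also still enters the convergence rule.

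**Conclusion.** The point holds as a mislabelled construct with a consequence for interpretation. The item validly records perceived momentary regulation effectiveness in real time. It lacks the property claimed for it in Measures and assigned to its layer in Data analysis strategy, and those passages conflict with Research design. Tau-U on this item can shift in either direction with no change in enactment, and baseline-trend correction does not prevent that.

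The size is unknown from the documents. The illustrative range of about −0.17 to 0.24 rests on assumed hard-day shares, a 2-point rating gap, SD 1 and independent days; it shows that the effect need not be trivial, not that it will occur. The mismatch itself needs none of these assumptions. The general confounding of an uncontrolled AB comparison is already conceded and is not the point here.

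**What to change.** 1. In Measures and in Data analysis strategy, describe the item as perceived momentary regulation effectiveness, and drop the terms enactment and mechanism-level for it and for the Tau-U series.
2. In the triangulation matrix, state that a Tau-U shift is not evidence of enactment. That evidence rests on the reflective notes and the third fidelity item. Add that Table 1 schedules the fidelity log from Week 1 and lists no reflective notes in the baseline weeks, so enactment has no Phase A comparison.

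Both changes are wording only, with no added burden on students or staff.

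Optionally, a brief daily item on whether a difficult moment occurred, asked in both phases, could serve as a descriptive covariate. Its costs should be named: it adds a response to a design with a 60% compliance threshold; a look-back question departs from the real-time intent; asking it in the baseline may rehearse what Week 1 trains; and reports of difficult moments may themselves change with the intervention. For that last reason, and because it would usually fall below the protocol's minimum of 10 Phase A points, Tau-U restricted to hard days should not be adopted.

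### Teacher and parent ratings are said to mitigate single-source bias, but the stated analysis and triangulation matrix do not use them

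*Protocol article*

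**What the plan says.** The Measures section of the protocol article acknowledges that its outcome indicators all come from student self-report, and adds two informant sources in response. For teachers: "Teacher behavioral ratings will be collected at pre- and post-intervention timepoints using a brief four-item adaptation of the Social Skills Improvement System". For families: "Parent or guardian reports will be collected using a parallel four-item brief form targeting home-context regulation and social behavior", at the same two timepoints. The role given to these data is stated as fact: "These informant sources provide convergent evidence from ecologically distinct observational contexts, reducing the sole reliance on student self-report". The same sentence goes on to say that they curb the inflation that comes from having one source.

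The Data analysis strategy describes a framework "structured to evaluate three outcomes: (a) trait-level directional movement, (b) state-level micro-trajectory change, and (c) mechanism enactment evidence". For the trait layer, "pre- and post-intervention changes in the BSCS and SSBS will be quantified using a within-subject standardized mean difference". The state layer is the EMA series, analysed by Tau-U. The third layer is deductive coding of qualitative material, which the Research design section limits to counselor fidelity logs and one-sentence student notes. A triangulation matrix is then built "to map (a) trait-level shifts, (b) state-level effect estimates, and (c) qualitative mechanism evidence". Agreement across these streams is taken to confirm that the intervention is feasible, and disagreement is taken as a sign that implementation has broken down.

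**The concern.** Collecting informant forms does not by itself reduce single-source bias. The protection arises only if the scores enter an estimate or the judgement of convergence. The article claims the protection in one section and sets out an analysis in another that gives the scores no place.

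What is at stake is how the matrix is read. The Limitations section names social desirability as a possible explanation of observed change. A student inclined to report improvement could move the BSCS, the SSBS, the EMA item and the written notes in the same direction. The matrix would then show convergence with no observed change in behavior behind it. Conversely, if teachers and parents saw no change, the matrix as stated could not register it.

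**Working it through.** The article gives no figure to reproduce. The check is whether the informant ratings are used anywhere after they are introduced.

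1. **Trait layer (Data analysis strategy).** The instruments named are the BSCS and SSBS, both completed by the student. Informant ratings: not used.
2. **State layer (Measures; Data analysis strategy).** This is one daily self-rating item. Informant ratings: not used.
3. **Qualitative layer (Research design; Measures; Appendix B).** The sources are counselor logs and student notes. The log has three items: nudges opened at least four times in the week, at least one note submitted, and at least one relevant behavior described by the student. The first two are usage records. They show engagement, not regulation or belonging. The third is recorded by the counselor, but its content is what the student described. Informant ratings: not used.
4. **Triangulation matrix (Data analysis strategy).** It maps the three streams above and has no informant stream.
5. **Missing data handling.** The trait outcomes are identified as BSCS and SSBS. No rule covers the informant forms.
6. **Table 1.** The pre entry lists BSCS/SSBS with consent, demographics and the EMA baseline. The post entry lists BSCS/SSBS. Neither lists a teacher or parent form.
7. **Elsewhere.** The Abstract and the quantitative design paragraph do not mention the ratings. The only other reference to parents in the methods concerns consent.

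Tally: 2 informant measures collected, used in 0 of 3 analysis layers and 0 of 3 matrix streams, listed in 0 of 2 outcome-assessment entries of Table 1, and covered by 0 missing-data rules.

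Scale of the collection: informants × timepoints × students is 2 × 2 × 40 = 160 to 2 × 2 × 60 = 240 forms if every form is returned. If post forms came only from students retained at the 80% threshold (an assumption), the count is 2 × 40 + 2 × 32 = 144 to 2 × 60 + 2 × 48 = 216. These figures count forms. They do not measure bias.

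**The case against.** The strongest reply is that this is an omission in a condensed article. No sentence says the ratings will be left out. The three layers are named as constructs, so pre-post informant scores on regulation and social behavior could sit under trait-level change. A full analysis plan, not shown, commonly settles how supporting measures are summarised. It follows that a reader should not infer that the ratings are excluded or that the mitigation can never be delivered. This part of the reply stands.

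It does not remove the point. The article itself names the trait instruments, in both the analysis and the missing-data sections, and it fixes the streams of the matrix and the meaning of convergence among them. An analysis plan that added an informant stream would change that published rule, and the mitigation claim is made in the article.

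A reader might also infer that everything in the matrix is student self-report. That goes too far: the counselor log contains usage records, and counselors may add a remark of their own. What is absent is an independent rating of behavior change.

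A third tempting inference is that the feasibility verdict as a whole is compromised. The documents do not support it. The four operational thresholds are recruitment of at least 70%, retention of at least 80%, median EMA compliance of at least 60% and fidelity of at least 75%. None is scored on self-rated improvement. The article also disclaims causal and efficacy inference.

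Table 1 is incomplete here but does not contradict Measures, which already sets the timing at pre and post.

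**Conclusion.** The point holds in limited form. The analysis as stated does not deliver the mitigation that Measures claims, because the teacher and parent ratings enter none of the three layers and none of the three matrix streams. The convergence judgement, which the article treats as confirming feasibility, can therefore rest on student-reported change with no independent rating of behavior to support or contradict it.

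The size of any resulting bias cannot be derived from the document. The conclusion rests on reading the article's named instruments and streams as the analysis intended; an unshown plan could already include the ratings. Because this is a feasibility study whose operational thresholds are untouched, the matter should be corrected but does not threaten the design.

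**What to change.** In the Data analysis strategy:

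- Summarise teacher and parent pre-post change with the within-subject standardized mean difference and 95% CI already chosen for the BSCS and SSBS.
- Add an informant stream to the triangulation matrix.
- State that convergence among student-derived streams without informant support is reported as single-source.
- State that disagreement between informants and students is reported descriptively and is not, on its own, read as implementation failure. Without this rule, the article's present reading of divergence would turn any disagreement between a teacher and a student into a malfunction.

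Add both forms to the pre and post entries of Table 1 and to the missing-data section. If the ratings are not to be used this way, withdraw the mitigation claim in Measures.

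The forms are already planned, so data collection is unchanged. The cost is a few more lines of analysis and the possibility that agreement across sources looks weaker. The choice should be fixed before data are seen, so that use of the informant ratings cannot depend on whether they agree with self-report.
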